## Introduction

Acute pancreatitis is a sudden onset inflammatory process of the pancreas, with variable involvement of local or remote organ systems. The annual incidence of acute pancreatitis in the UK is approximately 30 per 100 000 of the population.^1^ This equates to approximately 18 000 people developing acute pancreatitis every year in the UK.^1^ There has been an increase in the incidence of pancreatitis in the last two decades.^2^ Gallstones and excessive alcohol are the two main causes for acute pancreatitis in the UK.^3^ Increasing age, male gender and lower socioeconomic class are associated with a higher incidence of acute pancreatitis.^1^

The clinical manifestation of acute pancreatitis is believed to be caused by activation of inflammatory pathways either directly by the pathologic insult or indirectly by activation of trypsin, a protease which can break down the pancreas.^4^ The average 60-day mortality associated with acute pancreatitis is 6.4%.^1^ Deaths occur as a result of a massive fluid extravasation from the inflamed pancreas combined with a severe systemic inflammatory response in the early stage and mainly from local complications in the late stage.^5^ The systemic complications occurring in the early phase result in poor oxygen delivery to the tissues and include worsening of pre-existing illnesses such as heart or chronic lung disease. Local complications which occur in the later phase include pancreatic pseudocysts, infected collections and pancreatic necrosis. These early and late complications are the major causes of the mortality associated with acute pancreatitis.^6 7^ They are also largely responsible for the decreased health-related quality of life (HRQoL) and loss of work days following acute pancreatitis.^8^ Thus, acute pancreatitis has a major effect on UK society with its complications having a significant impact on patients, their next of kin and their employers.

Various pharmacological interventions have been evaluated in acute pancreatitis, but none are in current clinical practice.^9^ Supportive management in terms of maintenance of fluid and electrolyte balance remains the mainstay in the treatment of acute pancreatitis. Despite the key importance of fluid therapy, a recent systematic review has highlighted that there is a lack of information on the optimal fluid therapy in acute pancreatitis.^9 10^ There has also been a decline in research in treatments for acute pancreatitis in general.^11^

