Several secondary clinical, surgical, biochemical, safety and quality of life outcomes will also be collected. Mortality will be assessed as well. Clinical outcomes will include severity of pancreatitis as assessed by Glasgow score, proportion of patients with severe acute pancreatitis, necrotising pancreatitis, infected pancreatic necrosis, requiring ITU stay, requiring renal replacement therapy, requiring ventilation, requiring surgical interventions for complications related to pancreatitis and incidence of positive blood cultures. Resource use data for health economic analysis on length of hospital stay, length of ICU stay, and number of days ventilated, time to return to pre-pancreatitis activities, number of workdays lost (in those who work) and costs (NHS and personal social services perspectives) will be collected. HRQoL will be assessed using the well-validated EuroQol-5 Dimension (EQ-5D) questionnaire on admission as baseline and subsequently on days 7, 30 and 90. All complications of pancreatitis including treatment-related adverse events (postradiological and surgical complications as classified by Clavien-Dindo Classification) and serious adverse events related to intervention will be recorded up to discharge and at follow-up. Routine biochemical tests performed as part of clinical care including blood gases, liver function tests, clotting profile, renal function, amylase, full blood count and C-reactive protein (CRP) will be recorded on admission and daily up to 2 weeks and biweekly up to discharge. In addition, serum samples will be collected from participants in both groups on admission, 12, 24 and 48 hours’ time points and stored at −80° for future analysis of biomarkers in acute pancreatitis.

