### Follow-up

Participants will be followed for 90 days. All clinical and HRQoL outcomes will be measured up to discharge and specifically at 30 and 90 days by face-to-face or telephone follow-up. CRP will be measured at 24 and 48 hours and every 24 hours during the hospital stay as per routine clinical practice. Clinical outcomes on follow-up include cumulative hospital and ICU stay including readmissions, predefined complications including organ failure, severe pancreatitis, infected pancreatic necrosis, surgical interventions, development of sepsis, pulmonary oedema or acute respiratory distress syndrome as well as mortality. Resource use data include medications, planned and unplanned tests and procedures and use of allied healthcare professionals (eg, physiotherapy, occupational therapy). HRQoL will be assessed using a validated questionnaire (EQ-5D).

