### Data collection and analysis

Recruitment data which include number of eligible patients presenting to the emergency department, number of patients screened, number of patients consenting and number of patients randomised are recorded in a recruitment log in the emergency department. A Consolidated Standards of Reporting Trials diagram will be presented to provide a detailed description of participant numbers at each time point during the trial.^24^ A paper CRF is created for each participant enrolled into the study. The data collected on the paper CRF are then transferred to a secure online database using the Research Electronic Data Capture platform.

Since this is a feasibility study, all analyses other than recruitment rate and withdrawal rates should be considered exploratory. The two groups will be compared to ensure they have similar baseline characteristics (box 2) using means and SDs or medians and IQRs for continuous variables, as appropriate, and frequency counts and percentages for categorical variables.

Box 2Baseline characteristics of patientsThe intervention group and the control group should have the following baseline characteristics:Age.Sex.Ethnicity.Body mass index (BMI).Time since onset of symptoms.Presumed cause of pancreatitis.Comorbidities.Baseline observations.Baseline renal function.Baseline blood gas parameters.Glasgow severity score on admission.Intravenous fluids prior to intervention.

For the primary outcome, that is, feasibility, the proportion of patients who consent to be randomised and the rate of withdrawal from GDFT protocol will be presented with a 95% CI. The median number of complications, graded by the Clavien-Dindo Classification, in each group will be presented. The proportions of people with complications between the two groups will be presented and compared using appropriate statistical test and 95% CI.

For the secondary outcomes, among patients who participate in the trial, all clinical and surgical outcome measures will be presented for each group separately using the mean, SD, median, minimum and maximum for continuous outcomes and using frequencies and proportions for categorical variables.

Quality of life will also be summarised for each group using mean profile plots over time. The mean difference in quality of life scores between the two groups at 7 days up will be presented with a 95% CI.

Kaplan-Meier survival estimates and plots will be presented to compare survival rates between the two groups.

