
All other secondary outcomes collected over time will be summarised for each group using mean profile plots. Mean differences for continuous outcomes and difference in proportion for binary outcomes shall be presented, with appropriate 95% CIs, at 30 and 90 days.

The number and nature of adverse events shall be reported for each group. No formal comparisons between the groups will be made and no hypothesis tests will be carried out. The results will inform us how sensitive the outcome measures are and, along with other information, will be used to determine the primary outcome of a subsequent large RCT. The results will also inform a sample size calculation for the primary outcome chosen.

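### The only contrast fixed for continuous secondary outcomes is a mean difference; read as clinical benefit, this lets early death pass as a short hospital or ICU stay (minor)

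*Protocol article*

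**What the plan says.** Two sections of the protocol article list the durations. Outcome measures introduces them as resource-use items for the economic analysis: "length of hospital stay, length of ICU stay, and number of days ventilated, time to return to pre-pancreatitis activities", followed by workdays lost and costs. Follow-up places part of the same information under a clinical heading: "Clinical outcomes on follow-up include cumulative hospital and ICU stay including readmissions".

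Data collection and analysis sets the summaries. Clinical and surgical outcomes are to be "presented for each group separately using the mean, SD, median, minimum and maximum for continuous outcomes". For the remaining secondary outcomes collected over time, the contrast is: "Mean differences for continuous outcomes and difference in proportion for binary outcomes shall be presented, with appropriate 95% CIs, at 30 and 90 days". The same section names Kaplan-Meier estimation for survival only. It calls everything except the recruitment and withdrawal rates exploratory, and it says the results will help to choose the primary outcome of the later large trial and to calculate its sample size.

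Participants are followed for 90 days, and mortality is reported as an outcome in its own right.

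**The concern.** Hospital and ICU days have two uses here. As costs, days actually used are the right quantity whether or not the patient survives. As evidence that the patient did better, they are not, because a patient who dies on day 5 records a short stay. The Introduction treats shorter ICU and hospital stay as an expected gain from goal-directed fluid therapy, and Follow-up lists stay among the clinical outcomes, so the second use is intended.

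Time to return to activities has a different difficulty. A patient not back to normal at day 90 has a censored value, and a patient who dies never has one. A mean difference does not suit an outcome of that kind, and no time-to-event summary is named for it.

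The stake is what gets carried forward. The trial is meant to show how sensitive the candidate endpoints are, and Sample size calculation justifies 50 patients by the need to estimate an SD. A difference or SD for stay that mixes recovery with early death could mislead the choice of the next endpoint or its sample size.

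**Working it through.** The plan states no figure of its own on this point, so there is none to reproduce.

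**Inputs from the protocol article**
- 50 patients randomised 1:1, so 25 per arm (Sample size calculation).
- Average 60-day mortality of 6.4% (Introduction).
- Follow-up of 90 days (Follow-up).

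**Assumed inputs**
- Death on day 5 to 10, in a patient whose stay would otherwise have lasted 20 to 60 days.
- For return to activities, the values given in step 4.

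**1. How many deaths to expect**
- Per arm: 25 × 0.064 = 1.6. In total: 50 × 0.064 = 3.2.
- Chance of at least one death in the trial: 1 − 0.936^50 = 0.96.
- Chance that the two arms' death counts differ by two or more, with both binomial (25, 0.064): 0.37.
- The trial excludes patients who need immediate ICU care and those transferred with complications, so its mortality may be lower. At half the rate (assumed, 3.2%), 25 × 0.032 = 0.8 deaths per arm, and the chance of at least one in the trial is 1 − 0.968^50 = 0.80.

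**2. What a death does to mean stay**

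Shift in the arm mean = deaths × (stay had the patient lived − day of death) / 25.

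| Stay if alive (days) | Day of death | One death | Two deaths |
|---|---|---|---|
| 20 | 5 | 15/25 = 0.6 | 1.2 |
| 40 | 5 | 35/25 = 1.4 | 2.8 |
| 60 | 10 | 50/25 = 2.0 | 4.0 |

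Every shift is towards an apparently better result.

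**3. The same patients on days alive and out of hospital to day 90**

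A patient who dies in hospital during the first stay scores 0. Had the patient lived without readmission, the score would have been 90 − 20 = 70, 90 − 40 = 50 or 90 − 60 = 30. One death therefore lowers the arm mean by 70/25 = 2.8, 50/25 = 2.0 or 30/25 = 1.2 days. Here a lower value is worse, so the death now counts against its arm.

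**4. Return to activities**

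Assume that 22 of 25 patients recover after a mean of 30 days and that 3 have not recovered by day 90, with true times of 120 to 180 days.
- Fully observed: (22 × 30 + 3 × 120)/25 = 40.8, up to (22 × 30 + 3 × 180)/25 = 48.0.
- Set to day 90: (22 × 30 + 3 × 90)/25 = 37.2.
- Left out: 30.0.

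The arm mean is understated by 40.8 − 37.2 = 3.6 days at the least and 48.0 − 30.0 = 18.0 days at the most, depending on a handling rule that the article does not give.

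A two-arm illustration: take exponential times with medians of 30 and 45 days, so 12.5% and 25% have not returned by day 90.
- Restricted mean to day 90 = (1 − S(90))/rate, with rate = ln 2/median: 37.9 and 48.7, a difference of 10.8 days.
- Mean among those who returned = (restricted mean − 90 × S(90))/(1 − S(90)): 30.4 and 34.9, a difference of 4.5 days.

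The second contrast arises only if patients who have not returned are dropped.

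**The case against.** The case against is substantial, and much of it stands.

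- **Means are not the only summary.** A reader might infer that the plan relies on means alone. It does not: the median and range are planned for each group, and a median of 25 stays hardly moves with one or two early deaths. This largely protects the descriptive reading of stay. It does not change the contrast that carries the confidence interval. For return to activities, it helps only if patients not recovered are kept in.
- **No exclusion rule is stated.** A reader might infer that patients not recovered at day 90 will be dropped. Nothing in the article says so; they could be set to 90 or censored, and an analysis plan that is not shown may settle it. The 4.5 against 10.8 days is therefore illustrative and not a property of the plan.
- **Costs are not biased.** A reader might also infer that the indicative costs are wrong. They are not: mean days used, deaths included, is the correct quantity for costing.
- **Coverage is partly inferred.** The link from the mean difference to stay is well supported by Follow-up. For ventilator days and return to activities, it rests on reading them as other secondary outcomes collected over time.
- **Deaths are visible.** Mortality and survival curves by arm are reported alongside, so an imbalance in deaths could be seen.
- **The shift is small against noise.** With equal mortality, both arms are shortened alike in expectation. If the SD of stay is 10 to 15 days (assumed), the standard error of the difference is SD × √(2/25) = 2.8 to 4.2 days, more than one death's effect. Low precision does not change what the contrast measures, but it limits the practical harm.
- **The day-90 limit hardly touches stay.** It cuts stay or ventilation only in patients still in hospital or ventilated at that point.

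**Conclusion.** The point holds in a limited form. The one contrast fixed for continuous secondary outcomes is a mean difference, and it plausibly covers hospital and ICU stay as clinical outcomes. Read as benefit, that contrast credits early death. The size is about 0.6 to 2.0 days of mean stay per death under the assumed stays, with about 1.6 deaths per arm at 6.4% mortality and probably fewer in this population.

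For ventilator days and return to activities, the same contrast applies by inference. A mean difference is a poor fit to an outcome censored at day 90 and undefined after death, but the size of that distortion depends on handling that the article does not state.

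The documents do not support a claim that the stated methods are shown to give a biased result throughout. Severity is minor: the analyses are exploratory, the plan disclaims hypothesis tests in its group reporting, and no criterion under Progress to full trial uses these durations. It still merits a change, because the results are to guide the next trial's endpoint and sample size.

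**What to change.** 1. Keep raw hospital, ICU and ventilator days, with mean and median, for costing, and show them next to deaths by arm.
2. For clinical reading and endpoint selection, add days alive and out of hospital and ventilator-free days to day 90, with zero days credited after death.
3. For time to return to activities, replace the mean difference with cumulative incidence to day 90, with death as a competing event and patients not yet recovered censored at day 90.

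The main inputs are already collected: stay with readmissions, deaths, ventilated days and the 90-day contact. The sample size does not change. The cost is a little more analysis and a line explaining the composite beside raw stay.

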### Control (standard care group)

The choice of fluid type, volume and rate of administration on the first 48 hours of admission for patients randomised to the control arm will be decided by the clinical team caring for the patient in order to mimic a real-world situation. Cardiac output monitoring variables will be measured every 4 hours on the standard care arm during the first 48 hours, however, the results will be blinded to the clinical team. The choice of fluid type, volume and rate will be recorded in detail. All other clinical, biochemical and HRQoL outcome measures will also be recorded for standard of care patients as outlined in the ‘outcome measures’ section.

The Cheetah NICOM device (Cheetah Medical) is a CE (*C*
*onformité*
*E*
*uropéene*) marked device which has been purchased for this study and training has been arranged for all staff on the equipment and the associated fluid administration algorithm which will be a key component of the trial. The research team will follow hospital policy on signals for ICU outreach reviews and escalation of care to ICU. NICOM monitoring and outcome measures will be recorded in ICU for both control and GDFT arms.

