### Blinding

It will not be possible to blind the research or clinical team during the first 48 hours of the study. However, the participants, outcome assessors of HRQoL and statisticians will be blinded to the groups. Patient blinding will be aided by NICOM monitoring of both intervention and control groups but performing GDFT in the intervention group alone. NICOM data from the control group will be collected at the same time points as the intervention group and will not be available to the treating clinicians.

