### Trial management structure

A Trial Management Group (TMG) chaired by the chief investigator and comprising leads at different sites, ICU research nurses, the surgical team representative, research fellows, statistician, qualitative researchers and health economist will meet fortnightly to discuss trial progress and address issues in recruitment and delivering the intervention. Trial progress will be reported to independent data monitoring committee (DMC) comprising experts in acute pancreatitis, medical statistics and clinical trials every 6 months.

All serious complications and any mortalities will be immediately referred to the sponsor and reported to the TMG and independent DMC. The trial will be stopped in case of two or more treatment-related suspected unexpected serious adverse reactions.

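### Serious adverse events are recorded with a relatedness qualifier, so that item cannot be compared like for like between the arms

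*Protocol article*

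**What the plan says.** All references are to the protocol article.

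- **Outcome measures** has one sentence on event recording. It opens with a broad class, "All complications of pancreatitis including treatment-related adverse events", and ends with a qualified one: "serious adverse events related to intervention will be recorded up to discharge and at follow-up". No other section says that SAEs are recorded regardless of cause.
- **Data collection and analysis** reports adverse events by arm with no qualifier: "The number and nature of adverse events shall be reported for each group". The same paragraph rules out formal comparison and hypothesis tests.
- **Blinding**: "It will not be possible to blind the research or clinical team during the first 48 hours of the study". Participants, HRQoL assessors and statisticians are blinded. No blinded assessor of causality is named. GDFT is given in one arm alone.
- **Control (standard care group)** extends outcome recording to control patients: "All other clinical, biochemical and HRQoL outcome measures will also be recorded for standard of care patients".
- **Follow-up** lists clinical outcomes without reference to cause, among them organ failure and "development of sepsis, pulmonary oedema or acute respiratory distress syndrome as well as mortality".
- **Trial management structure** has an unfiltered reporting duty, "All serious complications and any mortalities will be immediately referred to the sponsor", and a trial stopping rule based on relatedness, "two or more treatment-related suspected unexpected serious adverse reactions".

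**The concern.** Safety of the intervention is a named secondary endpoint. In acutely ill emergency patients, it is often impossible to say of one serious event whether a fluid bolus caused it. Randomisation answers the question at group level, but only if events are counted in the same way in both arms.

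Making relatedness a condition of entry gives up that advantage for the SAE item. One arm's count becomes an attribution by people who know the allocation, and the other arm's count is zero by definition. The error can go either way: events attributed too readily make GDFT look harmful, and events not attributed hide a real excess.

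**Working it through.** The article states no figure on this point, and by its own account no formal sample size calculation was made, so there is nothing to reproduce. The check is mainly a comparison of sections, followed by an illustration of size.

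**Step 1. Who can contribute to the SAE item?** Table 1 labels GDFT as the intervention and standard care as the control, and the Blinding section confines GDFT to one arm. On that reading, an SAE related to the intervention can occur only in the GDFT arm.

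**Step 2. Which serious events have another route into the record?**

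| Type of serious event | Route without a relatedness filter? | Section |
|---|---|---|
| Complication of pancreatitis | Yes, both arms | Outcome measures |
| Organ failure, sepsis, pulmonary oedema, ARDS | Yes, both arms | Follow-up |
| ITU stay, ventilation, renal replacement, positive blood culture | Yes, both arms | Outcome measures |
| Death | Yes, both arms | Outcome measures; Follow-up; Trial management structure |
| None of the above, judged related to GDFT | SAE item only, GDFT arm only | Outcome measures |
| None of the above, not judged related, or in a control patient | None stated | – |

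The gap is the last row. Many events that come to mind do not fall there. A serious hospital-acquired infection would often appear as a positive culture or sepsis, and an electrolyte disturbance would often show in the routine blood results. The Introduction counts worsening of existing heart disease among the systemic complications, so some cardiac events enter that way. An example that may be lost is an arrhythmia managed on the ward, without organ failure or ITU transfer, that nobody calls a complication of pancreatitis.

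**Step 3. How far could the SAE item mislead?** The arm size of 25 is from the article. The true SAE rate p (equal in both arms) and the share r of GDFT events judged related are assumptions.

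- Expected SAEs, all causes: 25 × p in each arm
- Expected under the stated rule: 25 × p × r in the GDFT arm, 0 in control

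| p | All-cause, each arm | Stated rule, GDFT (r = 20%) | Stated rule, GDFT (r = 50%) | Stated rule, control |
|---|---|---|---|---|
| 10% | 2.5 | 0.5 | 1.25 | 0 |
| 20% | 5.0 | 1.0 | 2.5 | 0 |
| 30% | 7.5 | 1.5 | 3.75 | 0 |

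The true difference is zero in every row. In whole patients, with assumed counts: 5 v 5 with two GDFT events attributed is recorded as 2 v 0, and 8 v 3 with none attributed is recorded as 0 v 0. These describe the SAE item alone. Events that also meet a class with its own route in Step 2 would still be seen elsewhere. One patient is 1/25 = 4 percentage points of an arm, so a few attributions change the summary.

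**Step 4. What between-arm safety comparison remains?** Data collection and analysis compares the proportions with complications, with a 95% CI. Progress to full trial requires that the GDFT complication rate be no more than 10% above control at 90 days. Both can be computed without judging relatedness. With equal complication rates p in both arms, the 95% half-width is 1.96 × √(2p(1 − p)/25):

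- p = 10% (assumed): 1.96 × √0.0072 = 0.166
- p = 40% (assumed): 1.96 × √0.0192 = 0.272

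The comparison is imprecise, at about ±17 to ±27 percentage points, but it exists.

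**The case against.** A reader might infer that SAEs are captured only when related, and that the safety objective therefore cannot be answered by comparing the groups. The documents do not support that. The word *only* is not in the text. The qualified SAE class is added to a broad class of complications, and most serious harms expected here, including the pulmonary oedema and ARDS that excess fluid might cause, are recorded in both arms whatever their cause. Serious complications and deaths go to the sponsor without a relatedness filter, and a between-arm complication criterion governs progression. This part of the objection stands and sets the limits of the point.

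Three further arguments carry some weight:

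- *Intervention* is not defined for SAEs. Control patients also receive NICOM monitoring and fluids, and the article speaks elsewhere of surgical interventions, which can occur in either arm. The zero in control therefore rests on the natural reading and not on an explicit definition.
- The by-group adverse event report is descriptive and carries no relatedness qualifier, which may mean that broader capture was intended. If so, the two sections disagree and one needs correcting.
- SAE definitions and causality forms usually sit in the full protocol, which is not shown. That would excuse silence. Here the article is not silent: it states a recording rule with a qualifier. The reporting duty to the sponsor does not replace that rule, because it covers complications and deaths and concerns notification.

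**Conclusion.** The point holds in a limited form. As written, the SAE item cannot be compared like for like between the arms, and it fits poorly with the promise to report adverse events for each group. The loss is confined to serious events that are not complications of pancreatitis, listed outcomes or deaths, and that are not judged related. Safety can be compared in part through the unfiltered outcomes.

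The conclusion assumes that intervention means GDFT, that relatedness is judged by staff who are not blinded in the first 48 hours (the article names no one else), and that the full protocol does not already require all-cause recording. The counts in Step 3 show direction and possible scale. No section of the article supplies the rates behind them. The change is worth making because it is cheap and removes an avoidable attribution bias from a named secondary endpoint.

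**What to change.** Reword the sentence in Outcome measures along these lines: *all serious adverse events, whatever their cause, are recorded in both groups from randomisation to day 90; relatedness is recorded as a separate field and is not a condition for entry.* State what relatedness refers to (GDFT, monitoring or other procedures).

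Align the other two sections with this. Trial management structure should use the same event term as Outcome measures. Data collection and analysis should say that all-cause SAEs are reported by arm, with related SAEs as a subset. The trial stopping rule need not change for this purpose.

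The cost is CRF and protocol wording plus some additional SAE forms, in 50 patients whose follow-up already runs to day 90. No endpoint or sample size changes. If the full protocol and CRF already capture all SAEs, only the article's wording needs correcting.
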